#### **HISTORY OF PROTOCOL UPDATES**

| VERSION    | DATE              | RAISON DE LA MISE À JOUR                                                                                                                                                                          |
|------------|-------------------|---------------------------------------------------------------------------------------------------------------------------------------------------------------------------------------------------|
| 1.0 | June 2011  | Version submitted to the Malian ethical committee, Bamako                                                                                                                                  |
| 2.0 | 2016/03/13 | Error corrected in the paragraph page 11 (Sample size calculation):
It is assumed that in the reference group, the value of HbA1c is 8.5% and with a standard deviation of 2.0 . |

## II - Describe the main institution/organization responsible for the project

NGO "Appui au développement, Santé Diabetes Mali (SDM)" was created in 2001, following the first work completed, in Mali, with the International Centre in Agronomic research for Development (CIRAD), on the diabetes Mellitus in Mali. SDM is an association of international solidarity. SDM is a non governmental organization (NGO), is a sustainable development association favouring projects that use a participative step.

SDM works in very close partnership with the Ministry of Health, the national direction of health, medical specialists and associations of diabetic patients in Mali. SDM is recognized and supported by the Malian government. This support was officialized by the signature of a master/ executive agreement with the Malian government on September 23, 2003.

"Appui au développement, Santé diabète Mali" is implementing different projects in Mali to improve the management of diabetes in Mali:

- Prevention of diabetes « Sensitizing, information of the public Malian on the diabetes Mellitus» will have as its aim to increase awareness and inform the general population about diabetes, its causes, consequences and how it can be treated. This will be done by using various tools to inform, educate and communicate specific messages to improve the knowledge of the general public and community and family leaders. One axis target specifically awareness in schools
- Training health professional and care restructuring: this axe is designed to train health professional to decentralize the management of diabetes in 5 regions in Mali. It is also aimed at providing the drug and testing equipment to ensure that these consultations may be decentralized.
- "Strengthening the associations of diabetic patients." This axe aims to boost existing diabetic patients associations and to form associations in areas with decentralized care for diabetes and without associations.

In addition to these axis, the NGO Santé Diabète Mali has developed several research projects on the problem of diabetes in Mali. This research has concerned:

- Research on the property of food eaten in Mali
- Research on the impact of traditional medicines
- Research on metabolic complications in the long term for the ARV
- Development of work on the economic impact of diabetes

Our NGO currently manages more than 15 contracts with various international donors including the European Union and various international cooperation agencies. Our NGO has therefore the organization, procedure manuals and mechanisms for the activities monitoring and the management control needed.

The NGO Santé Diabète Mali (SDM) has very deep relations with the International Diabetes Federation. SDM has organized workshops for the IDF Africa Region (example: in 2006 SDM has organized the seminar on policies to fight against diabetes in Africa that gathered 75 participants from 17 African countries). It also takes part in several projects for the IDF (guideline for africa, economic impact study).

#### IV - Describe the supporting institutions

##### **National hospital Point G – endocrinology and diabetology unit – Bamako – Mali**

The hospital will realize the implementation and monitoring of the project in Mali in collaboration with the NGO Santé Diabète Mali (SDM). The strict collaboration between national hospital and University Hospital will permit to have support by the epidemiology department of the Faculty for the processing and data analysis

##### **PAEDI Research Center – Clermont-Ferrand – France** PAEDI [Process of Actions in Education:

Determinants and Impacts] works on adult learning and context influences: professionalisation, practices' analysis, learning in plri-linguistic context, intergration of sociocultural, psychological, and language specificities in learning. In the field of Health and patient education, PAEDI works on the differentiated access to knowledge and educational tools in chronic diseases and the problematics of social variations, low literacy and precarity. .This team has developed the methodology of education using the "Learning Nests" and will support the university hospital in Bamako and the NGO Santé Diabète Mali to adapt the tools to the Malian and the development of this approach in health education.

##### **CHR of La Reunion island - Endocrinology and Metabolism (Felix Guyon Hospital) Endocrinology and Diabetology in La Reunion**

[name] and his team has implemented in different outpatient settings (in La Reunion, France and Mauritius) the development of self management courses for patients, using the Learning Nests approach intimately coupled with medical care and follow-up. This team brings the expert support in diabetes, training and organization of the implementation of actions in diabetes education.

## 2. Non-technical summary

The project will test the implementation of a specific methodology for education of type 2 diabetic patients that will be set up using patients involved (peer educators) and 3 guides developed specifically for the therapeutic education of type 2 diabetic patients. This project will take place in 1 sites in mali : the capital Bamako. 75 diabetic patients will be subjected to intervention with this methodology and 75 other diabetic patients will be the control group. At various stages of the project, we will analyze the impact on biological, anthropological constants, etc ... of the group undergoing the intervention compared to the control group.

## 3. Scientific abstract of proposed study

##### **Title of project:**

A randomized trial of an intensive education intervention using a network of involved diabetic patients (peer educators) to improve glycemic control of type 2 diabetic patients

##### **Research question (s)/hypothesis:**

Main objective of the research: compare the improvement of HbA1c 1 year after an intervention led by peer educators, versus a conventional care in health centre

Secondary objectives:

Study the evolution of bio clinical parameters: fasting glucose, weight, BMI, blood pressure, waist size

**Method (s) :**

This study will be conducted by a multidisciplinary team that brings together high level skills in research projects and in peer education projects. It will be conducted in one site in one country Mali. This site was chosen because they meet a functional care, access to medicines and a dynamic association of diabetic patients. Peer educators and persons targeted by the project will be recruited through the local association of patients. This association will be a social support that provides on going prevention counseling, education and support services to people who have diabetes. It represents an important link between patients, educators and general medical services. The procedure will start by the training of peer educators who were identified and recruited to facilitate the sessions. Then, the 4 educational sessions: control of cardiovascular risk (blood pressure, waist circumference, smoking, cholesterol, glycaemia), control of Food (balance, fat, carbohydrates), physical activity management, insulin management, will be carried out and patients will be able to:

- Analyze knowledge that appears in various forms, including forms adapted to illiterate patients (colour codes, presence of photos)
- Act on knowledge: the patient observes, makes hypothesis, he experiments, compares, deduces, analyzes, makes relations.
- Work in interaction with other learners, which gives education a social dimension.
- Decide on the implementation of actions taking into account individual, cultural, social, economic context

For each situation, a day of training will be conducted by trained peer educators with theoretical contributions on the issue, practical scenarios, analyzes of the issues out of frame and put in "educational security ". These training days will be implemented with 8-10 patients (1Hour and an half) and the 4 sessions will take place over a period of two months starting from the inclusion of patients.

2 groups of 75 persons will be formed. One group will have specific education using methodology of learning nests. The other group will be a control group not subject to this specific education. To evaluate, we propose a classical randomized controlled experimental (RCT) design, with randomization at the person-level. For outcome measures, we propose change in HbA1c, increase of social and emotional support and increase of linkage to clinical care. In addition to HbA1c, we propose measuring changes in systolic, diastolic blood pressure, and weight.

**Public health significance :** It is very important to find an education methodology adapted to the African context. This line of diabetes management is essential to improve the management of African diabetic patients.

**Sustainability plan:** If the evaluation of this methodology is conclusive, the Malian state will implement the methodology in the 22 diabetes units of the country.

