**Activité Physique**

**JE MARCHÉ 30 MINUTES PAR JOUR**

7

Points à gagner

Points gagnés

Total = \_\_\_\_ / \_\_\_\_

Je choisis cette action ☐

- 1 • Assistance in daily management and living with diabetes : the provision for patients of supports understandable and discussed in situation facilitates the appropriation of knowledge over time: the written materials are discovered, approached and negotiated in situation, with the help of the educator. The patient takes the written materials at home, and keeps them carefully for the possibility of organizing the monitoring and the daily management of his diabetes and his life over the long term.
- 2 • Social and emotional support: the methodology of patients and educators recruitment through patients' associations and educational clubs will provide a very strong social and emotional support to patients. The group education methodology will also allow patients to support each other. Indeed, the work in interaction with other students, gives education a dimension allowing a very strong emotional support. The possibility of keeping the written material negotiated and worked in situation (booklets), will disseminate information within the family or/and in the social network of the trained patient (without risk of knowledge transformation, as the booklet is a reference). This possibility increases the number of people informed on the prevention of chronic diseases, prevention of complications but also allow bringing the necessary information to the family and social network of the formed patient which will strengthen the social and emotional support brought to the patient.

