### **Comparison group**

The group subjected to educations will follow the whole process of peer education described in Part 1 of this Protocol.

The control group will perform these "classic" individual consultations but will not follow the whole process of peer education.

The classical management in diabetes consultations consists of:

- A counselling session
- A measure of blood glucose
- A measurement of blood pressure
- A measure of weight and size
- A complete clinical examination
- A prescription or a renewal of treatment (diabetes pills, insulin, IEC, statins etc ...)

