## STATISTICAL METHODS USED

The data will be analyzed by a medical epidemiologist with the Epi Info software.

Initially, we will proceed to the description of the included patients and compare the characteristics of both groups of patients to detect any differences at inclusion. These characteristics are expressed as percentage for qualitative variables and as mean and median and their dispersions parameters, respectively, standard deviation and interquartile 25 and 75. The comparison of characteristics between the two groups will be performed using appropriate tests, the exact X2 or Student's t-test. Then, a uni-variable analysis of variance analysis type will be conducted to identify variables to include in the multivariable explanatory models. The inclusion threshold chosen will be 0.25. Data will be expressed as means  $\pm$  SD unless indicated otherwise. Comparisons within groups were performed using analysis of variance by comparing the averages using the comparison test of averages or the Student's t-test.

The comparison between groups will be conducted by analysis of variance, using the Bonferroni correction where appropriate. The results will be statistically significant at  $p < 0.05$ .

**Direct beneficiaries in Mali:** The 150 diabetic patients directly reached by the activities / The 15 peer educators trained in the action areas selected in Mali. The 25 health agents of the action areas selected in Mali / Families and relatives of patients reached by animations (10 000 persons)

**Indirect beneficiaries in Mali :** All the diabetic patients of Mali (3% of the adult population) / All the health workers involved in the management of diabetes in Mali / The Malian health systems / The Malian population by reducing the risk factors of diabetes and increasing the quality of life

**Indirect beneficiaries in Africa:** Diabetic patients of French and English speaking African countries which will benefit from the methodology and tools developed

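### The analysis and sample size make no allowance for clustering by education group in the intervention arm; if outcomes correlate within groups, the standard error is understated

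*Supplement*

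**What the plan says.** Allocation is by patient: the abstract's Method(s) section proposes a controlled trial "with randomization at the person-level".

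Delivery in the intervention arm is by group. The same section says "a day of training will be conducted by trained peer educators" for each topic, and "These training days will be implemented with 8-10 patients (1Hour and an half". The list of beneficiaries after the statistical section counts "The 15 peer educators trained in the action areas selected in Mali".

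Mutual influence is an intended part of the method. Learners are to "Work in interaction with other learners, which gives education a social dimension", and the description of social and emotional support says "The group education methodology will also allow patients to support each other".

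The other arm has no such structure. The Comparison group section says: "The control group will perform these 'classic' individual consultations but will not follow the whole process of peer education".

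On analysis, Statistical Methods Used plans Student's t-test, analysis of variance and multivariable models with covariates screened at 0.25. For the treatment comparison: "The comparison between groups will be conducted by analysis of variance, using the Bonferroni correction where appropriate". Neither that section nor Calculation of the Size of Study mentions an ICC, a design effect, a random effect or a robust variance for education group or educator. Results are judged at p < 0.05, and no confidence interval is named.

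**The concern.** This is a partially nested design: patients are randomized one by one, but after randomization one arm is gathered into groups and the other is not. People who attend the same sessions, discuss choices together and share an educator may end up with more similar HbA1c changes than people from different groups. The protocol's own account of how the education works makes that plausible.

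A t-test or one-way analysis of variance counts 60 intervention patients as 60 independent pieces of information. If outcomes are positively correlated within groups, they carry less than that. The computed standard error is then too small, p-values are too low, and the power is below what the calculation implies. The abstract says a conclusive result would lead to adoption in 22 diabetes units, so the p-value matters.

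**Working it through.** **Inputs from the Supplement.** Target difference 1 percentage point of HbA1c; SD 2.0; alpha 5%; power 80%; 60 analysed and 75 recruited per arm (Calculation of the Size of Study). Groups of 8-10 (Method(s)).

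**Assumed.** Two-sided test; total SD 2.0 in both arms; each patient stays in one group; ICC 0.01, 0.02, 0.05 or 0.10, since none is given.

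**Step 1: the plan's own figure.** n per arm = 2 × 2.0² × (1.96 + 0.8416)² / 1² = 62.8, so 63 (64 by the t-test), against 60 stated. SDs of 2.0 and 0.5 give (4 + 0.25) × 7.849 = 33.4, so 34. The loss step reproduces: 60 / 0.80 = 75. Power at 60 per arm and SD 2.0: SE = 2 × √(2/60) = 0.365; Φ(1/0.365 − 1.96) = 78.2% (77.5% by the t-test). The gap between 60 and 63 is a separate matter. No variant contains a clustering allowance.

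**Step 2: number of groups.** 75/10 = 7.5 and 75/8 = 9.4, so about 8 to 10 groups.

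**Step 3: effect of clustering in one arm.** For group size m:
- Design effect in the intervention arm: DE = 1 + (m − 1) × ICC.
- Variance inflation of the difference: (1 + DE)/2.
- Actual type I error of the nominal 5% test: 2 × [1 − Φ(1.96 / √inflation)].
- Power allowing for clustering: Φ(1/SE − 1.96), with SE = 2 × √((1 + DE)/60).

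Example, ICC 0.05 and m = 9: DE = 1.40; inflation = 1.20; true SE / computed SE = 1.095; type I error = 7.4%; SE = 0.400; power = Φ(0.54) = 70.5%.

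| ICC | DE (m = 8 to 10) | True SE / computed SE | Actual type I error | Power, 60 per arm |
|---|---|---|---|---|
| 0 | 1.00 | 1.00 | 5.0% | 78% |
| 0.01 | 1.07-1.09 | 1.02 | 5.4-5.5% | 77-76% |
| 0.02 | 1.14-1.18 | 1.03-1.04 | 5.8-6.1% | 75% |
| 0.05 | 1.35-1.45 | 1.08-1.11 | 7.1-7.7% | 71-70% |
| 0.10 | 1.70-1.90 | 1.16-1.20 | 9.2-10.4% | 65-62% |

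**Step 4: check by simulation.** The unadjusted t-test on data with group effects varying around a zero mean (20,000 runs per setting, 60 or 75 per arm, m = 8 or 10) rejected in 5.3-5.6%, 5.8-5.9%, 7.0-7.5% and 8.9-10.2% of runs for the four ICCs, and in 4.7-5.1% at ICC 0.

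**Step 5: sensitivity to group size and SD.** If 20% of a group of 9 is lost, 7.2 remain. At ICC 0.05, DE = 1 + 6.2 × 0.05 = 1.31, inflation 1.155, type I error 6.8%, power 72.2%.

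If the SD of 0.5 is the intervention-arm SD, the clustered arm contributes little variance and the inflation becomes (4 + 0.25 × DE)/4.25. For m = 8 to 10 the type I error is then about 5.1% at ICC 0.01, 5.2-5.3% at 0.05 and 5.5-5.6% at 0.10, and power at 60 per arm stays near 96%.

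**The case against.** A reader might infer that the type I error does exceed 5% and that the trial's confidence interval will be too narrow. The documents do not support either as a fact.

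- **Conditional on the ICC.** None is given. At 0.01 the loss is about half a point of alpha and one to two points of power. Because allocation is by patient, a test under the strict null, where the education affects nobody and creates no correlation, keeps its 5%. The excess arises when group or educator effects vary around a zero average. This stands, and limits the claim.
- **No planned interval.** The statistical section names p-values only. The point reaches an interval only if one is derived from the same model. This stands.
- **Equal SDs.** The calculation assumes 2.0 in both arms. The meaning of the 0.5 is unclear, and reading it as the intervention-arm SD nearly removes the effect. That reading does not reproduce 60 per arm either, so it is a caveat, not a rebuttal.
- **Stable groups.** No section says that patients keep the same group or educator. Fifteen educators for about 8 to 10 groups, with no stated assignment, leave the educator structure unknown. If membership changes between sessions, a single group identifier describes the data imperfectly. This is a further reason to record both.

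None of this shows that the plan allows for clustering, and none reverses the direction of the error when the correlation is positive. Nor is it a detail left to a missing analysis plan: the protocol states its method, and that method assumes independence.

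**Conclusion.** The point holds in conditional form. The omission is certain: one arm is taught in interacting groups, and neither the analysis nor the sample size takes this into account. The size of the consequence is not known from the documents. For an assumed ICC of 0.01 to 0.10, equal SDs and stable groups of 8-10, the nominal 5% test has an actual type I error of about 5.4% to 10.4%, and power at 60 analysed per arm is about 77% to 62%. The starting value of 78%, rather than 80%, is not due to clustering. Confidence is high on the omission and its direction, and moderate at best on its size. The plan should be changed, but the trial's design does not need to be.

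**What to change.** 1. Record the education group and the educator for every intervention patient at each session, and keep group membership fixed where possible.
2. Analyse the HbA1c change with a partially nested linear mixed model: a random education-group effect in the intervention arm only, each control as an independent unit, a separate residual variance for each arm, and Satterthwaite or Kenward-Roger degrees of freedom. The arm-specific variance also covers the uncertainty about the SD of 0.5.
3. Restate the power in Calculation of the Size of Study under a stated ICC, with a range, and leave enrolment at 75 per arm.

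**Cost.** Two extra data fields and a different model. The stated power will look less favourable: at ICC 0.05 and SD 2.0, 80% would need 74-77 analysed per arm, against the 60 planned. With only about 8 to 10 groups the group variance will be imprecisely estimated and may come out at zero, and the small-sample degrees of freedom will widen the error bars somewhat. Another package will be needed if Epi Info cannot fit the model. Randomization and delivery of the sessions otherwise stay as they are.

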## 4. Details of application

**Main objective**

Compare the improvement of HbA1c 1 year after an intervention led by peer educators during 12 months associated with conventional care, versus standard care alone in clinic, for 120 people with type 2 diabetes in Sikasso Mali.

**Secondary objectives**

- 1 - To compare the intermediate evolution of the HbA1c (3, 6 and 12 months)
- 2 - To compare the evolution of the bio-clinical parameters at 3.6, and 12 months: weight, BMI, blood pressure, waist measurement

**Background information about project including current evidence in the field and literature and Indicate how the project addresses the community's need for diabetes care prevention.**

Education on diabetes is known through several names: 'education of the patient', 'patient's therapeutic education', 'self management education' etc...[1]. All these terms question about the diabetic person's place in a continuous progress involving permanent communication with a care team and the coordination of a care program [2]. Therapeutic education is a necessary component of an integrated care process for people with diabetes. Diabetes is a complex condition, which requires an effective medical management from caregivers and a good autonomous management from the person with diabetes. This dual approach helps to promote choice of healthy lifestyles, improve the quality of life and reduce direct and indirect health costs for society [3]. Educational approaches set up must recognize the critical and fundamental role of psychosocial factors for effective diabetes education [4], [5]. In 1914, Elliott Joslin published a book in which he stressed the importance of training nurses to participate to the education on diabetes and its management [6]. In 1936, insulin appeared and specialized nursing in diabetes had expanded. It became clear that nurses should develop their skills when it comes to education and counselling as well as expertise in clinical care [7]. The publication of the DCCT studies results in 1993 and UKPDS in 1998 amended the diabetes care, from the simple reduction of glycaemia and blood pressure, to the active prevention of complications and in to the intensification of treatment [12] [13]. It was a turning point in the role of diabetes educator. In developed countries, diabetes educators began by considering the key aspects of the insulin doses adaptation, of the changes in eating habits and of the screening for complications, paving the way for the work of specialised nurses and of other caregivers, such as dieticians, chiropodist in diabetes education [8]. Several studies have highlighted, in developed countries, the challenge for health professionals to implement education activities for patients. Above the consideration of the different cultural contexts, the barriers often described by professionals for the establishment of effective patient education are the availability of time and the inadequacy of the initial and continuing training [9]. At hospital, the particular context in which education situations took place do not necessarily encourage the effective setting up of prevention and health practice in every day life [10][15]. In the context of African health systems that combine low human and financial resources with a very important turn over of staff, it is very difficult to establish specific curricula for diabetes educators, but also to mobilize health staff specifically for this task [16]. In these particular settings, the involvement of peers in the assistance in daily management and living with diabetes, the Social and emotional support and the Linkage to clinical care seems to be a perfect tighten to complement the organization of diabetes care in these countries. The reviews of several studies have shown the very positive results of this approach that can be implemented by following several methodological models [11] [12] [13]. For this study we have chosen to implement and evaluate the impact of the methodology: The Learning Nests approach: Group Education focusing on understanding of key concepts and interactions with social context [14] [15] [16]. This approach developed by health professionals and human sciences seems to be the best suited for the socio economic and cultural contexts which are encountered in Africa. It is based on 5 principles- the building and setting up of learning situations which are based on scientific data of the medical and social/human sciences frame (socioconstructivism, knowledge construction, adult learning principles): - The integration of the context of life in developing the educational situation - The work on the operational dimension (use of the knowledge for the action, decision making by the learner), with the support of individual booklets (for the teacher and for the learner) -The intimate coupling of the educators training and the educational situations for learners - The implementation in a long-term program, with precise indicators of results

**Aims:** To evaluate the effectiveness and sustainability of diabetic patient-based (peer educators) education program in Bamako (Mali) using a randomized trial, with 150 type 2 diabetic patients

**Global method:** the purpose of this methodology is to set up coordinated training and education activities targeting populations with diabetes based on a pragmatic approach (the learning nests methodology) of appropriation and construction of knowledge that takes into account the individual, social, economic, cultural context. This work is being implemented on the basis of group modules

specifically designed in their running: are studied the concrete elements of knowledge to mobilize, patients' actions, the role of health the educator, indicators of progress and monitoring during sessions and on the long term. Each patient is gotten to consider the elements involved in his/her disease, and the actions that can be achieved taking into account the feasibility in his/her own context. The education monitoring is envisaged through a data compendium present in the individual booklets that are given to patients at the end of each education session. The animations sessions will allow:

- Patients to appropriate knowledge that is essential to better manage chronic disease.
- Patients to understand diabetes and reduce cardiovascular risk by learning how to manage their treatment, diet and regular physical expenditure.
- Patients to stake and analyse the elements of their environment, their representations and ordinary habits with the knowledge coming from the medical field. This analysis of elements in presence should allow everyone to take relevant and appropriate decisions (family, culture, economic, social network). In practice the implementation of the methodology takes place in 4 stages:
- 1 - The training of peer educators who have been identified and recruited to lead the animations
- 2 - An initial cycle on the themes of knowledge and control of cardiovascular risk (BP, cholesterol, blood sugar, waist measurement, diabetes, treatment and complications).
- 3- An initial cycle on the subject of food controlling (balance, fat, carbohydrates).
- 4- An initial cycle on the themes of physical activity.

During each education session, interactive workshops will allow to work on: a balanced diet, carbohydrates in the diet, cardiovascular risk and understanding of diabetes. For each situation, a one-day training will be conducted by trained peer educators with theoretical input on the issue dealt with, put in practice situation, analyses of issues outside the framework in "safety education". These training days will be implemented with patients (1H 30) and 3 meetings will take place over a period of 2 months. An educational replay will be made 6 months after, 12 after and 18 months after. The educational booklets will be available for patients at the end each meeting. It is important to that the tools used in this methodology allow for accessibility of learning by people with low literacy rates. It allows also the reproducibility of the education sessions because these sessions are designed and supervised, with brochures for patients, guides for teachers, and indicators of learning during the course.

